#### Anthropometric measures

For anthropometric assessments, participants will be asked to attend in light clothing with shoes removed. Body height and weight will be assessed using the Seca 777 digital column scale (Seca, Germany). Waist and hip circumference will be measured using the Seca measuring tape 201 (Seca, Germany). All measurements will be taken based on the standard procedures and measured twice to get the average readings. The BMI will then be calculated and recorded.

#### Knowledge and self-efficacy

The CVD-related knowledge will be assessed using the Attitudes and Beliefs about Cardiovascular Disease (ABCD) risk questionnaire which has been validated in the Malaysian population (Woringer et al., 2017; Mat Said et al., 2022). This questionnaire may assess the accuracy of perceived CVD risk, overall knowledge of CVD, and the intention to modify behaviour concerning diet and exercise.

The Medication Understanding and Taking Self-Efficacy (MUSE) scale will be used to assess medication-taking and understanding self-efficacy, as medication adherence can reduce the risk of developing CVD (Cameron et al., 2010; Appalasamy et al., 2019). This scale assesses various aspects of medication management, including understanding instructions, remembering to take medications, and integrating medication use into daily routines.

#### Lifestyle behaviours

Physical activity will be assessed using the International Physical Activity Questionnaire (IPAQ) (Craig et al., 2003; Chu & Moy, 2015). The IPAQ provides a comprehensive overview of a participant’s physical activity patterns, allowing for the categorisation of individuals into different activity levels and assessment of sedentary behaviour. The Perceived Stress Scale (PSS-10) (Cohen et al., 1983; Al-Dubai et al., 2014) will be used to assess the perceived stress level of participants as chronic stress can contribute to the development and exacerbation of CVD risk factors (Kivimäki & Steptoe, 2018). Other information on lifestyle behaviours including smoking habits, alcohol consumption and sleep duration will also be obtained from participants as these behaviours can influence CVD risk factors (Kaminsky et al., 2022).

#### Dietary intake

The dietary intake will be assessed using the short food frequency questionnaire, while nutrient intake will be assessed using 24-hour dietary recall (Johansson, 2014). For the dietary recall, the participants will be asked about details of the foods and beverages consumed in the past 24 h, including the types of food, cooking methods, estimated portion size and brands. The recalls will be made for weekdays and weekends using the multiple-pass approach (Gibson, Charrondiere & Bell, 2017). A food album (Suzana et al., 2015) and household measurement tools will facilitate food portion estimation.

#### Process evaluation

The peer attendance will assess the adherence to the program to each peer session. The program feedback will be recorded in a self-administered questionnaire post-program (T1), assessing the participants’ satisfaction with the content satisfaction and peer leaders. We will use a five-factor instrument to determine content satisfaction: time and place for peer session, module objective, module content, module structure, and module relevance. In addition, peer leadership will be assessed with a three-factor instrument: peer interactions, peer leader readiness, and peer leader knowledge. The responses will be recorded using a Likert scale with scores ranging from 1 (strongly disagree) to 5 (strongly agree). The sum of the responses for each domain (content and peer leadership) reflects the participants’ satisfaction, with higher scores indicating a higher level of satisfaction (Mahadzir et al., 2020).

### Statistical analysis

Data analyses will be conducted using the Statistical Package for the Social Sciences (SPSS) version 28.0 (IBM Corp., USA). Nutrient intakes from 24-hour dietary recalls will be analysed with Nutritionist Pro software (Axxya Systems, USA) to yield total energy, macronutrient and micronutrient intakes, then transferred to SPSS for analysis. Other data obtained from the assessment will be directly entered and analysed using the SPSS software. Descriptive statistics will be calculated for each variable. Continuous variables will be expressed as a mean with standard deviation (SD) or median with interquartile range. Frequencies and percentages will be obtained for categorical variables. Independent t-test or equivalent will determine differences between the study groups for continuous variables. McNemar and Chi-Square tests will be performed for similar comparisons for categorical variables. Comparison of changes in outcome measures at T0, T1 and T2 between study groups will be analysed using two-way repeated measures analysis of covariance (ANCOVA) to adjust for any baseline differences in key variables. Correlation analyses will be performed between satisfaction and adherence, with changes in outcome measures at T1 and T2.

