### Participant allocation

Two groups will be under study for this quasi-experiment: the intervention group and the control group. The recruited participants will be allocated into one of the two groups based on their geographical location to ensure participants’ convenience when participating in the intervention activities. The participants in the intervention will be further divided into five subgroups, each consisting of six to seven members based on their peer connectivity. The non-random allocation considers familiarity and peer support, which are expected to lead to higher engagement levels in the intervention activities, promoting better adherence to the intervention and potentially more significant lifestyle behavioural changes.

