### Outcome measures

The primary outcome of this study is the change in FRS, which is calculated based on age, sex, levels of high-density lipoprotein cholesterol (HDL-C) and total cholesterol, systolic blood pressure (SBP), smoking habit and the presence of diabetes. This risk calculator has been validated in the Malaysian local population and is recommended for assessing and managing the global risk of individuals in primary prevention of cardiovascular disease (CVD) (MOH, 2017).

The secondary outcomes include changes in body weight, body mass index (BMI), waist circumference, hip circumference, fasting blood glucose (FBG), low-density lipoprotein cholesterol (LDL-C), triglycerides (TG) levels, diastolic blood pressure (DBP), Medication Taking and Understanding Self-efficacy (MUSE), attitudes and beliefs about CVD, physical activity level, lifestyle habits (smoking, alcohol consumption and sleep duration), stress level, edible oil use and dietary intakes.

A process evaluation will be conducted at T1 among the intervention participants to assess their adherence to the program and satisfaction towards content and peer leadership.

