### Data collection

Study researchers will administer a pretested, structured questionnaire in both Malay and English language to collect data of the outcome measures at T0, T1 and T2. Sociodemographic data and medical history will be collected at T0 only. At T1, the program feedback form and questionnaire on content satisfaction will be administered among the intervention participants.

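### McNemar is assigned to comparisons of unmatched groups, and the remaining between-arm test for categorical secondary outcomes, a chi-square at one visit, ignores baseline in a non-randomised design

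*Protocol article*

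**What the plan says.** All of the relevant text is in the Materials & methods part of the protocol article.

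- **Statistical analysis, continuous variables:** "Independent t-test or equivalent will determine differences between the study groups for continuous variables".
- **Statistical analysis, categorical variables (the next sentence):** "McNemar and Chi-Square tests will be performed for similar comparisons for categorical variables".
- **Statistical analysis, change over time:** "Comparison of changes in outcome measures at T0, T1 and T2 between study groups will be analysed using two-way repeated measures analysis of covariance (ANCOVA". The stated purpose of the covariate adjustment is to allow for baseline differences. The sentence covers outcome measures without separating continuous from categorical ones.
- **Outcome measures:** the secondary outcomes are changes, and include "physical activity level, lifestyle habits (smoking, alcohol consumption and sleep duration), stress level, edible oil use and dietary intakes".
- **Lifestyle behaviours:** the activity questionnaire is described as "allowing for the categorisation of individuals into different activity levels and assessment of sedentary behaviour".
- **Participant allocation:** participants are "allocated into one of the two groups based on their geographical location". No matching of individuals is described.
- **Data collection:** the questionnaire is used to "collect data of the outcome measures at T0, T1 and T2", so each outcome is measured three times per person.

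The Discussion lists allocation by geography as a limitation that may bring selection bias, because people in different areas may differ in ways that affect the outcomes.

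**The concern.** The phrase about similar comparisons can only point back to the sentence before it, which concerns differences between the study groups. McNemar tests whether the two off-diagonal counts of a paired table are equal. It has no meaning for two separate sets of people.

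If McNemar was meant for change within each arm, the text can be followed, but a problem remains. McNemar then never compares the arms. Chi-square does compare them, but at one visit and without regard to where each arm started. The plan's own device for baseline adjustment, the ANCOVA, is a model for continuous outcomes.

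Lifestyle behaviours are part of the study aim. For an outcome handled as a category, following the stated tests could turn a difference between the two areas at T0 into an apparent intervention effect at T1 or T2. It could also invite the inference that a change significant in one arm and not in the other is an effect.

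**Working it through.** The plan gives no figure on this point, so there is none to reproduce. The check has three parts.

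**1. The tests set against the data they would meet**

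| Stated test | Data it needs | Compares arms? | Uses baseline? |
|---|---|---|---|
| McNemar | Pairs (same person, two visits) | No | Within arm only |
| Chi-square | Independent groups, one visit | Yes | No |
| Two-way repeated measures ANCOVA | Continuous outcome, T0, T1, T2 | Yes | Yes, but not suited to categories |

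No row gives a baseline-adjusted comparison between arms for a categorical outcome.

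**2. Chi-square at follow-up when the areas differ at T0**

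Inputs from the Sample size justification: 28 per arm (calculated minimum) and 34 per arm (recruited), two-sided 0.05. The prevalences and rates of change are assumptions, because the article gives none. No intervention effect means that both arms share the same probabilities of leaving the category (10%) and entering it (5%).

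Follow-up prevalence = baseline × (1 − 0.10) + (1 − baseline) × 0.05:

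- 60% baseline: 0.54 + 0.02 = 0.560
- 50% baseline: 0.45 + 0.025 = 0.475
- 30% baseline: 0.27 + 0.035 = 0.305

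Standard error of the difference = √(2 × p̄ × (1 − p̄) / n), with p̄ the mean of the two prevalences. Rejection probability ≈ P(Z > 1.96 − difference/SE). The last column is a simulation with 4,000 runs per scenario and an uncorrected chi-square.

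| Baselines | n per arm | Difference | SE | Ratio | Approximate rejection | Simulated |
|---|---|---|---|---|---|---|
| 50% v 30% | 28 | 0.170 | 0.130 | 1.30 | 26% | 24.0% |
| 50% v 30% | 34 | 0.170 | 0.118 | 1.44 | 30% | 30.8% |
| 60% v 30% | 28 | 0.255 | 0.132 | 1.93 | 49% | 47.6% |
| 60% v 30% | 34 | 0.255 | 0.120 | 2.12 | 56% | 57.4% |

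The result depends on the assumptions. With 50% v 30% and 30% leaving the category, simulated rejection is 18.2% at 28 per arm and 22.3% at 34. With equal baselines of 50%, it stays at 4.3% to 5.3%. The excess therefore comes from the baseline difference, and the test itself is sound between independent groups.

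**3. Reading an effect from separate McNemar tests**

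Let p be the power of McNemar within each arm when both arms truly change equally. The chance of significance in the intervention arm and not in the control arm is p(1 − p):

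- p = 0.20: 0.20 × 0.80 = 16%
- p = 0.50: 0.50 × 0.50 = 25%, the maximum
- p = 0.80: 0.80 × 0.20 = 16%
- p = 0.05 (at most, with no true change): 0.05 × 0.95 = 4.75%

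The nominal error in one direction is 2.5%. A simulation with 50% baseline in both arms, 5% entering and 30% or 40% leaving gave significance in exactly one arm in 24.1% and 43.8% of runs at 28 per arm, and in 34.2% and 50.5% at 34. By symmetry, half of each figure (about 12% to 25%) falls in the direction favouring the intervention, in line with the formula.

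**The case against.** The strongest reply is that this is one loose sentence. Chi-square, named in the same breath, is a valid test between independent groups, and the ordinary reading is McNemar within group and chi-square between groups. A condensed article may also leave models for categorical secondary outcomes to an analysis plan.

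Much of this stands. A reader might infer that the categorical results would rest only on a wrong test or on separate within-arm tests. The documents do not support that, because chi-square is named. The missing model would not be a finding by itself either. What remains is that the stated between-arm test ignores baseline, while the same section asks for baseline adjustment and the Discussion warns that the areas may differ.

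A reader might also infer that smoking, alcohol and activity are all categorical outcomes. The article fixes no scale for them. Activity or alcohol analysed as a quantity would come under the ANCOVA, as would sleep duration. The activity questionnaire is said to allow categorisation, which describes the instrument and does not define an endpoint.

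Two further limits hold. Nothing in the article says that an effect will be inferred from significance in one arm only, so part 3 of the check describes a risk and not a planned step. Having three visits does not rule out McNemar within an arm, since it can be run for T0 to T1 and for T0 to T2.

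**Conclusion.** The point holds in a limited form. As worded, McNemar is assigned to a comparison where it cannot be used. On the charitable reading, the only suitable between-arm test stated for any secondary outcome analysed as categorical is an unadjusted chi-square at one visit.

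With no intervention effect and assumed baselines of 50% v 30% or 60% v 30%, that test would reject in roughly 24% to 57% of trials at 28 to 34 per arm (10% leaving and 5% entering the category), and in about 18% to 22% in the one milder scenario examined. Inferring an effect from significance in the intervention arm only would err with probability 16% at 20% or 80% within-arm power, and at most 25%.

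These sizes rest on assumed prevalences and rates of change. The article says only that the areas may differ, not that they will. The primary outcome, change in FRS, is continuous and untouched. This should be corrected, but it does not threaten the main result.

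**What to change.** In the Statistical analysis section:

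1. Restrict McNemar to descriptive change within each arm, and name the visit pairs.
2. Restrict chi-square, or Fisher's exact test, to describing the groups at a single visit.
3. State which secondary outcomes will be analysed as categorical.
4. For those, estimate the intervention effect either with a GEE or mixed logistic/ordinal model over T0, T1 and T2, reporting the group-by-visit term, or with logistic regression at T1 and T2 adjusted for the T0 value.

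Choose one option in step 4 before the data are seen, because the two answer slightly different questions when baselines differ. In the 50% v 30% example, equal transition rates still give changes of −2.5 points (47.5 − 50) and +0.5 points (30.5 − 30). Neither option removes confounding by area beyond what the baseline value carries, so the limitation in the Discussion stays.

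The cost is a change of wording and a little more analysis work on data already collected, in software that can fit these models (SPSS GENLIN or GENLINMIXED). At 28 to 34 per arm, sparse categories may need collapsing or a simpler model.

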**Methods::**

A minimum total sample of 68 low-income community members at risk for CVD will be recruited and allocated either to the control group or the intervention group. Participants in the control group will receive standard lifestyle advice and printed materials for CVD prevention, while the intervention group will participate in the 8-week MYCardio-PEER intervention program. The participants will be assessed at Week 0 (baseline), Week 8 (post-intervention) and Week 20 (post-follow-up).

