#### Sample size justification

The sample size for the quasi-experiment was calculated using the G * Power 3.1 sample size calculator software (Faul et al., 2009). Based on expected changes in the FRS with a medium effect size of 0.25, the minimum number of participants required in each intervention and control group is 28, giving this study 80% power at a significance level of 0.05 (two-tailed test). Considering the prospective nature of the study and attrition rate of 20%, a minimum number of 34 participants will be recruited into each study group.

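### The repeated measures ANCOVA over T0, T1 and T2 leaves the primary change in FRS undefined and, run in the usual way, discards Week 8 data from anyone lost before Week 20

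*Protocol article*

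**What the plan says.** The Outcome measures section states: "The primary outcome of this study is the change in FRS". It names no visit. The abstract and the Study flow section give two follow-up assessments, Week 8 (T1, end of programme) and Week 20 (T2, after 12 weeks without active intervention). Study flow gives them different purposes: T1 for the proximal effect of the programme, T2 for whether effects last.

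The Statistical analysis section gives one method for between-group change, for all outcomes alike: "Comparison of changes in outcome measures at T0, T1 and T2 between study groups will be analysed using two-way repeated measures analysis of covariance". The covariates are there "to adjust for any baseline differences in key variables", and these variables are not listed. The software is SPSS 28.

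The Sample size justification section works from an effect size of 0.25 on changes in FRS, without saying which change, and allows for an "attrition rate of 20" per cent, raising 28 per group to 34.

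**The concern.** Two features of the fixed text matter.

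- **What is tested.** T0, T1 and T2 are all listed as outcome times. The natural test of changes between groups is then the group-by-time interaction, an omnibus test over two independent contrasts. The protocol has two separate questions (did FRS fall by the end of the programme, and did the fall last), and this test answers neither by itself. With two candidate changes and none designated, the choice of which to call primary stays open until the data are seen.
- **Who is analysed.** The standard SPSS repeated measures procedure needs a value at every visit. A participant measured at T0 and T1 but lost by T2 contributes nothing, not even at T1. In a study of 68 people that is a material loss. It may also distort the comparison, because contact differs by arm: the intervention group has weekly peer activity, while controls are contacted only for re-assessment. Reasons for dropping out could therefore differ.

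The role of T0 FRS is also unsettled. It is an outcome level in the model, and it could also be one of the unnamed adjustment variables.

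**Working it through.** **Inputs from the protocol article.** Two groups; three visits; 28 per group required, 34 recruited; 20% attrition; effect size 0.25; 80% power; two-tailed 0.05.

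**Assumptions (not in the document).** Equal SD at each visit, equal correlation of 0.7 between any two visits, and effects in SD units of FRS.

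**1. The plan's own figures.** 28 × 1.2 = 33.6, rounded up to 34, which is the stated number; 28 / 0.8 = 35, a difference of one. After 20% loss, 34 × 0.8 = 27.2, so about 27 per group have all visits. If instead 20% missed each follow-up visit independently, 34 × 0.8 × 0.8 = 21.8, about 22 per group. The 28 itself can be neither confirmed nor refuted, because neither the test nor the correlation is given. The calculation therefore does not reveal which change in FRS was intended.

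**2. Degrees of freedom.** Group by time: (2 − 1) × (3 − 1) = 2.

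**3. What the 2-df test can distinguish.** With n per group and group differences e at (T0, T1, T2), the noncentrality is (n/2) × Σ(e − mean e)² / (1 − ρ). Take n = 27, ρ = 0.7 and error df = 52 × 2 = 104.

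| Group difference (SD) at T0, T1, T2 | Σ(e − mean e)² | Noncentrality | Power |
|---|---|---|---|
| 0, 0.5, 0.5 (sustained) | 1/6 | 13.5 × 0.1667 / 0.3 = 7.5 | 67% |
| 0, 0.5, 0 (gone by T2) | 1/6 | 7.5 | 67% |
| 0, 0, 0.5 (late only) | 1/6 | 7.5 | 67% |
| 0, 0.5, −0.5 (reversed) | 1/2 | 13.5 × 0.5 / 0.3 = 22.5 | 99% |

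The first three patterns are equally detectable, and a reversal is the most detectable of all. The p-value cannot tell them apart.

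**4. Possible bias from keeping completers only.** No true effect, control dropout random, and the intervention arm loses exactly its 7 participants with the worst T1 change (a ceiling).

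- SD of change: √(2 × (1 − 0.7)) = 0.775.
- Fraction kept: 27/34 = 0.794, so the normal cut-off is 0.821 with density 0.285. Mean shift among those kept: 0.285 / 0.794 = 0.359 SD of change.
- At T1: 0.359 × 0.775 = 0.28. Simulation at the actual sample size gives 0.27.
- At T2: the slope of T2 change on T1 change is 0.3 / 0.6 = 0.5, so the bias is half that at T1, about 0.13.

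| Dropout pattern | Spurious benefit at T1 | at T2 |
|---|---|---|
| Random in both arms | 0.00 SD | 0.00 SD |
| Same outcome dependence in both arms | about 0.00 | about 0.00 |
| Moderate dependence, intervention arm only | 0.14 | 0.07 |
| Worst T1 changers lost, intervention arm only | 0.27 | 0.13 |

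These figures are for change from T0. Adjusting for T0 FRS can reduce them: in a separate simulation at correlation 0.6, a T2 bias of 0.11 became 0.06.

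**5. Precision lost at T1.** Suppose all losses fall between T1 and T2, and the true T1 effect is 0.5 SD adjusted for T0 FRS (residual SD √(1 − 0.49) = 0.714). Power for the T1 contrast, by normal approximation, is 82% with all 34 per group and 73% with 27 completers.

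**The case against.** **The article is silent on missing data.** This is true. Dropping incomplete participants is the usual behaviour of the named procedure, not plan text, and imputation or analysis sets may be laid out in a document not shown. The point rests on the method that the article does fix, and the data loss follows only if that method is run in the usual way.

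**Follow-up contrasts may be defined elsewhere.** They may be. But the visit at which the primary outcome is judged belongs in the outcome definition, and the Outcome measures section leaves it out. The article also does not label the ANCOVA a primary analysis; it is simply the only method given for comparing change.

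**Repeated measures ANCOVA is a recognised method.** It is, and with complete data a mixed model would add little beyond clarity. The case for change rests on the expected attrition and the undefined contrast.

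Three stronger readings are tempting, and the documents support none of them.

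- *The analysis is biased by the 20% dropout.* The 20% is a planning allowance with no stated mechanism, timing or pattern by group. Under random dropout, or the same outcome-related dropout in both arms, the bias is about zero.
- *The omnibus test wastes power.* Not in general. For an equal effect D at T1 and T2 under equal correlations, the sum of squares is 2D²/3 for the omnibus test against D²/2 for the T0-to-T1 contrast, so its noncentrality is 4/3 as large. Where the contrast has 80.0% power, the 2-df test has 83.7%. The weakness is interpretation, not power.
- *Including T0 dilutes the group main effect.* The text speaks of comparing changes, which points to group-by-time. Nothing suggests that the main effect would be the test.

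**Conclusion.** The point holds with limits. As written, the protocol article does not say which change in FRS is primary, and its one stated method gives a 2-df test that cannot separate a sustained benefit from a transient or reversed one. That follows from the text and needs no assumption.

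The loss of data is a property of the procedure as normally run: about 27 of 34 per group analysed at the planned attrition, with T1 values discarded for anyone lost later. The result is at risk of bias, with an illustrative range of 0 to about 0.27 SD at T1 and 0 to about 0.13 SD at T2. That range assumes no true effect, a visit correlation of 0.7 and, at its upper end, an extreme dropout pattern confined to the intervention arm. The change should be made; it does not make the design unworkable.

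**What to change.** In the Outcome measures and Statistical analysis sections:

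1. Name one primary contrast, for example the between-group difference in FRS change from T0 to T1, with T0 to T2 as the key secondary contrast for persistence. The investigators may prefer the reverse; what matters is choosing before the data are seen.
2. Analyse FRS with a linear mixed model (SPSS MIXED) on all available data, with group, visit, group-by-visit and an unstructured within-person covariance.
3. Give T0 FRS one role only: a baseline covariate with T1 and T2 as outcomes, or an outcome level with contrasts on change. List the other adjustment variables by name.

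**Cost.** Wording only; no new data, software or participants. Two downsides should be acknowledged. One time point becomes secondary, and the model relies on data being missing at random given what was observed, which the data cannot verify.
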